### 5.4 Withdrawal criteria

Withdrawal criteria will include:-

---

\* prior chloroquine ingestion will not be an exclusion criterion. Drug ingestion in the previous 2 weeks will be ascertained by patient interview as full testing for all locally available drugs with antimalarial activity is not feasible.

1. withdrawal of consent or non-compliance with assigned study regimen;
2. appearance of other species of *Plasmodium*;
3. vomiting within one hour after re-dosing;
4. protocol violation.

If it is necessary to withdraw a patient during the treatment phase, administration of the study drug will be discontinued. If the patient is still parasitaemic, quinine will be given as a rescue therapy unless there are clinical reasons to use another drug. For withdrawals outside the treatment phase the team will carry out all the safety and efficacy assessment measurements that would have been carried out at the next scheduled visit and the same will apply at delivery (unless the patient is lost to follow up). In such cases the study conclusion page in the Clinical Report Form will be completed and the study medication records updated. Patients withdrawn from the study will continue attending routine antenatal care provided by the MCH clinic. Finger prick blood smear for microscopy and Hb. will be done at every withdrawal. If rescue treatment is given, the blood smear will be checked again on day 7 post-treatment to ascertain parasitological clearance. Patients withdrawn before day 7 and not classified as treatment failures will be replaced.

5) Patients who fail on treatment will be treated with rescue treatment and counted as treatment failures (see above).

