#### **6.4 Adverse events (other than treatment failure)**

a) If a patient is unable to tolerate the trial medication the reason for discontinuation will be recorded in the Clinical Record Form as an “adverse event” and alternative rescue medication initiated.

b) Any clinical or laboratory abnormality which in the opinion of the senior attending clinician might be or is likely to be due to the study medication will be recorded as an adverse event.

Quinine at a dose of 10-mg/kg body weight will be the rescue medication for those who require it.

Adverse events will be classified according to:

|                                     |                                                                                                                                                           |
|-------------------------------------|-----------------------------------------------------------------------------------------------------------------------------------------------------------|
| Severity                            | a) non-severe, b) severe                                                                                                                                  |
| Causality in relation to medication | a) not related, b) unlikely to be related, c) possibly related, d) probably related, e) most probably related, f) insufficient data/information to assess |

Subjects with an AE will be followed up until the condition has disappeared or stabilized.

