## 7 Sample size and duration of study.

**NOTE ADDED Oct 2004- the sample size calculation in italics is the original one. There is a revision following slow recruitment due to local control measures. This is in normal font and blue.**

*Sample size has been calculated based on treatment failure as defined in section 4.1. If the response of pregnant women to antimalarial treatment is similar to that of children in Muheza, the proportion of women with treatment failure by day 28 in the SP+Placebo group will be at least 45%, the parasitological clearance failure rate among sick children at the study site ([name] et al., 2001). A Cochrane data review of studies of amodiaquine in Africa showed a day 14 clearance failure rate on amodiaquine alone was 17% (Olliaro and Mussano, 2000) leading to a theoretical failure rate for SP+Amodiaquine of at least 8% ( $0.45 \times 0.17$ ) if there is no interaction between these drugs. In the Gambia, day 14 failure rate with SP+Artesunate was 1.6% (von Seidlein et al 2000). Assuming the 28-day failure rate of 4% with artesunate alone, the failure on amodiaquine+artesunate is estimated at at least 1% ( $0.17 \times 0.04$ ). In this study, it is assumed that the best treatment would achieve 5% failure rate. We will consider anything up to 10% failure rate to be equivalent for public health purposes.*

*Allowing for a 10% defaulter rate approximately 40 women per group would be sufficient to detect a five fold decrease in the risk of treatment failure in the three combination groups compared to the SP group. However this sample size is insufficient for comparing the risk of treatment failure between the different combinations. It is important to compare the efficacy of SP+ amodiaquine versus the combination including artesunate as the latter combination is likely to be more expensive and hence advantage over the former needs to be defined. Thus, in order to detect a 4 fold difference in treatment failure between SP+Amodiaquine and amodiaquine+artesunate group (eg 8% vs 2%) with 95% precision and 80% power, we will enrol 80 women in the SP+placebo group and 240 women in each of the other three groups.*

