## **9 Stopping rules/discontinuation criteria (finalised after meeting of the DSMB)**

*Parasite clearance:* The study has to balance the Tanzania government's recent policy to use SP as first line drug treatment against a high SP-resistance in Muheza district. We assume that around 45% of women in the SP group will need escape medication. Since all women will be admitted to the study ward, the escape medication will be administered on time and complications arising from the use of a relatively ineffective drug should be minimal. However, if the proportion of women needing escape medication is  $\geq 40\%$  in any arm of the study, we will discontinue that arm when 50 women are enrolled which will give a confidence limit of 25-55% for the estimated treatment failure rate.

*Side effects.* All serious possible side-effects and foetal deaths will be faxed to the DSMB statistician. All other adverse events will be forwarded. The DSMB (see section on ethics) will decide on whether one arm, or the whole study, needs to be terminated. Suggested guidelines for this following the first meeting of the DSMB is that the DSMB would take note following one SAE in an arm, and consider whether an arm needed to be terminated after 2, but would review in the light of data at that stage. The DSMB wishes to be informed if there is a fall in haemoglobin of  $>4$  g/dl, OR where haemoglobin falls below 5 g/dl and these will be treated as a potential SAE, but since most such drops will be secondary to the natural history of the disease these will be noted and discussed, but treated differently from other SAEs.

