## **11. Data analysis.**

The primary outcome will be by treatment defined as having at least one dose of study drug. A secondary analysis will be by intention to treat defined as being enrolled into the treatment log and assigned a number. Treatment failure as defined in section 4.1 is the primary outcome.

Other pre-planned analyses are:

- Fetal viability;
- Birth outcome 6 weeks after due date;
- Parasite clearance rate at day 3;
- Parasite recrudescence or reinfection rate by day 14;
- Fever clearance rate (time);
- Level of recovery of Hb on day 14;
- Adverse events;
- Relapse confirmed by PCR.

Planned stratified analyses are by parity and HIV serostatus.

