| Adverse Event Review                              | ✓                           | ✓              | ✓              | ✓                      | ✓  | ✓  | ✓  | ✓           |                                  |
| Concurrent Medication Review                      | ✓                           | ✓              | ✓              | ✓                      | ✓  | ✓  | ✓  | ✓           |                                  |
| Malaria Finger-prick blood smears                 | ✓ b              | ✓ b | ✓ b | ✓                      | ✓  | ✓  | ✓  | ✓           | ✓                                |
| Blood Sample for Parasite DNA                     | ✓                           |                |                |                        |    |    |    |             | ✓                                |
| HIV test                                          | ✓                           |                |                |                        |    |    |    |             |                                  |
| Clinical Chemistry                                | ✓                           |                |                | ✓ c         |    |    |    |             |                                  |
| Haematology                                       | ✓                           |                |                | ✓                      |    |    |    |             |                                  |
| Routine urinalyses                                | ✓                           |                |                | ✓                      |    |    |    |             |                                  |
| Treatment with study drug                         | ✓                           | ✓              | ✓              |                        |    |    |    |             |                                  |
| Placental and Newborn investigations d |                             |                |                |                        |    |    |    | ✓           |                                  |
| Assessment of new-born e               |                             |                |                |                        |    |    |    |             |                                  |

a. Temperature to be monitored every 12 hours until the temperature falls below 37.5 °C and remains normal for at least 24 hours.

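### Section 5.4 and Appendix 1 can be read as ending or thinning adverse-event follow-up at treatment failure, in conflict with section 6.6, and the SP arm would lose most

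*Protocol*

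**What the plan says.** **Withdrawal rules.** Section 5.4 of the Protocol closes its withdrawal criteria with item 5: "Patients who fail on treatment will be treated with rescue treatment and counted as treatment failures (see above". It says nothing about later visits. The replacement rule just before it covers women withdrawn before day 7 who are not classed as failures, which implies that failures are among the withdrawn. For withdrawals outside the treatment phase, 5.4 provides the measurements due at the next scheduled visit, the same again at delivery, and a completed study conclusion page. After rescue it adds a smear on day 7. Withdrawn women then continue in routine antenatal care.

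**Schedule.** In Appendix 1 the row "Adverse Event Review" is ticked on days 0, 1, 2, 7, 14, 21, 28 and at delivery, but is blank in the treatment-failure column. So is the row for concurrent medication. Examination, foetal viability, vital signs, symptoms, smear and parasite DNA are ticked there.

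**Follow-up.** Section 6.6 asks discharged patients to attend on days 7, 14, 21 and 28, with tracing of those who do not come. It makes no exception for failures.

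**Harm recording and analysis.** Section 6.4 is headed "Adverse events (other than treatment failure". Section 4.1 item 1 counts convulsions, persistent vomiting, renal impairment, respiratory distress and specified haemoglobin falls as failure when they lead to rescue. Section 11 lists "Adverse events" and foetal viability as planned analyses, with no time window.

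**Expected failure.** Section 9: "We assume that around 45% of women in the SP group will need escape medication". The sample size section says that failure on SP "will be at least 45%, the parasitological clearance failure rate among sick children at the study site". It gives per cent figures for SPAQ ("leading to a theoretical failure rate for SP+Amodiaquine of at least 8") and AQAS ("the failure on amodiaquine+artesunate is estimated at at least 1").

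**The concern.** Treatment failure happens after randomisation, and the plan expects it far more often on SP than on SPAQ or AQAS. If adverse-event review ends or thins out at failure, the arms are observed for different lengths of time. A regimen that fails often would then collect fewer late adverse events for a reason unrelated to its toxicity. The loss may also be informative, because women who fail have persistent or recurrent infection, which the Background section links to foetal loss.

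The trial is justified by the lack of safety data on these combinations in pregnancy. Visit rules and the assessment schedule are protocol matters, and staff at the site could apply either reading.

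**Working it through.** **1. The plan's own figures.** SPAQ: 0.45 × 0.17 = 0.0765, stated as 8%. AQAS: 0.17 × 0.04 = 0.0068, stated as 1%. Both reproduce, and both are given as minimum values. The revised 72 per arm (1% against 15%) reproduces with two-sided alpha 0.05, 80% power and a continuity correction, reading the stated β of 0.8 as power. Lapdap has no planning rate. The only figure is 7% uncleared in an earlier local study, so Lapdap is left out of the arithmetic.

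**2. Expected failures per 72 women.** SP 72 × 0.45 = 32.4; SPAQ 72 × 0.08 = 5.8; AQAS 72 × 0.01 = 0.7. At the revised plan's upper rate: 72 × 0.15 = 10.8.

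**3. Share of the four reviews (days 7, 14, 21, 28) lost.** Loss = failure rate × (reviews missed ÷ 4). The documents do not give the day of failure, so each row assumes that all failures fall on one day. Section 5.4 does not say whether the next-visit measurements are made at withdrawal or on the next visit date, so both cases are shown.

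| Failure at | Later review held | Missed | SP (45%) | Arm at 15% | SPAQ (8%) | AQAS (1%) |
|---|---|---|---|---|---|---|
| Day 7 | none | 3/4 | 33.8% | 11.3% | 6.0% | 0.75% |
| Day 14 | none | 2/4 | 22.5% | 7.5% | 4.0% | 0.5% |
| Day 7 | day 14 | 2/4 | 22.5% | 7.5% | 4.0% | 0.5% |
| Day 14 | day 21 | 1/4 | 11.3% | 3.8% | 2.0% | 0.25% |
| Day 28 | none due | 0 | 0 | 0 | 0 | 0 |

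Criteria 2 and 3 of section 4.1 are read on day 3. If all failures fell there, the SP loss would be 0.45 × 4/4 = 45% with no later review, or 0.45 × 3/4 = 33.8% with the day 7 review held. That is an extreme case outside the range used below.

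**4. The same in days.** Mean days observed to day 28 = (1 − p) × 28 + p × t, where p is the failure rate and t the day recording ends.
- t = 7: SP 0.55 × 28 + 0.45 × 7 = 18.6; SPAQ 26.3; AQAS 27.8. SP has 70% and 67% of the other two.
- t = 14: SP 0.55 × 28 + 0.45 × 14 = 21.7; SPAQ 26.9; AQAS 27.9. SP has 81% and 78%.
- t = 28, or failures kept on the schedule: 28 days in every arm.

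**The case against.** **No passage says that recording stops.** This is correct. A reader might infer from item 5 that harm recording ends at failure and that SP women are followed for less time as a matter of fact. The text does not support that. Item 5 requires only rescue and counting as a failure, and section 6.6 taken alone keeps these women on the schedule. What remains is a conflict between 5.4 with Appendix 1 on one side and 6.6 on the other.

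**Foetal viability is protected.** This is largely right. It is ticked in the treatment-failure column, and section 6.3 requires it at each follow-up visit. Only checks after the failure visit are in doubt.

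**The secondary endpoints have a window.** Foetal death (item 1) and other adverse events (item 11) in section 4.2 are limited to the treatment period, which mostly precedes failure. Those comparisons are essentially unaffected. The section 11 analyses carry no such limit.

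**Other safeguards exist.** Birth outcome is sought for all mothers. Recorded adverse events are followed until they resolve or stabilise. Serious possible side effects and foetal deaths go to the DSMB. These stand, but following a known event does not detect a new one.

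**The section 6.4 heading excludes nothing.** One might infer that events scored under 4.1 item 1 are barred from the adverse-event record. They are not: 6.4(b) records any abnormality that the senior clinician thinks might be due to study drug, and section 9 flags large haemoglobin falls. The heading can still mislead, so a clarifying sentence is useful.

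**The blank cell rarely matters.** Failure found at day 7 or day 28 coincides with a visit where adverse-event review is already ticked. The blank bites on failures found between scheduled visits, and it does not settle what happens afterwards.

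**The direction of bias is uncertain.** This is fair. Shorter follow-up would favour SP, but rescue quinine, which the Background calls often unpleasant, would add events mainly in the SP arm.

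**Conclusion.** The concern holds conditionally. The Protocol contradicts itself on whether women who fail keep their day 7 to day 28 adverse-event review, and the expected failure rates make the answer matter unequally by arm.

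Under the withdrawal reading, and for failures from day 7 on, the SP arm loses between 0 (failure found at day 28) and about 34% (failure at day 7, no later visit) of the four reviews. If the next-visit assessment is held, the loss is about 11% for failure at day 14 and 22% at day 7. The corresponding losses are at most 6% for SPAQ and under 1% for AQAS at their stated minimum rates, and about 11% for an arm failing at 15%. Under the section 6.6 reading nothing is lost.

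These sizes rest on the plan's assumed failure rates and on an assumed day of failure. They apply to the adverse-event and post-failure foetal-viability analyses of section 11. They do not apply to the endpoints limited to the treatment period or to birth outcome.

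**What to change.** 1. Reconcile 5.4 with 6.6: state that women who fail keep adverse-event review and foetal-viability checks at all remaining scheduled visits to day 28 and at delivery, in every arm.
2. In Appendix 1, tick adverse-event review and concurrent-medication review in the treatment-failure column.
3. Keep the heading of 6.4, but add that clinical events meeting 4.1 item 1 are also recorded as adverse events and that parasitological failure alone is not. Deleting the heading's qualifier would be too broad, since it could turn symptom-free parasitaemia at day 28 into an adverse event.
4. Report adverse events to day 28 by allocated arm, and separately up to the first rescue dose. The first table keeps follow-up equal across arms; the second shows events before rescue quinine could add any.

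No treatment changes. The cost is a short amendment, a few more attended visits among those already scheduled, and one extra table.

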## **6. TREATMENT OF PATIENTS**

### **6.1 Study regimens**

*Choice of drugs:* On 5th April 2001, WHO/RBM convened a meeting of experts to discuss and decide on possible alternative chemotherapeutic drugs to SP for the treatment of malaria in non-pregnant patients in areas of SP resistance. Using a pre-set selection criteria, the meeting arrived at 4 possible alternatives and based on currently available information, ordered the combinations in order of current preference as:-  
artemether-lumefantrine (Co-artem)> amodiaquine + 3-days artesunate (AOAS3)> SP + 3-days artesunate (SPAS3)>SP + amodiaquine (SPAO) (WHO 2001).

This trial will investigate two of these four options. The investigators consider that a randomized trial of the sort proposed is probably not the appropriate vehicle for investigating artemether-lumefantrine at this stage. Although animal toxicity studies showed no teratogenic effects at doses  $\geq 100$  mg/kg of the combination (although some embryotoxic effects were seen), and lumefantrine alone shows no evidence of mutagenicity at doses up to 1000 mg/kg (Novartis 2000), there are no existing studies involving lumefantrine-containing regimens in pregnant women. Of the other regime not tested as it now looks unlikely that the SP/artesunate combination will be deployed in areas where SP resistance is significant.

SP/amodiaquine and amodiaquine/artesunate have been chosen as useful alternatives to S/P which would be affordable locally. Officials from the Ministries of Health (MoH) in the sub-region who participated in the 13th EANMAT Secretariat meeting (June 2001) in Dar-es-Salaam, ranked these combinations as highly appropriate for the sub-region and worth testing (*Minutes, EANMAT Sec13 in Dar-es Salaam*). S/P has been assessed in pregnancy (Verhoeff *et al* 1998, Parise *et al* 1998, Shulman *et al* 1999) and is now recommended for intermittent treatment in pregnancy.

Both artesunate and artemether have been given to many pregnant women (often inadvertently), and current published data demonstrate no evidence of human teratogenicity (McGready *et al* 1998). Follow up of over 539 women seen in Thailand who received an artemisin for treatment

of malaria in pregnancy showed no adverse effects on the mother or on her baby (McGready *et al* 2001). Following WHO recommendations (1995) artemisinin derivatives have been used for malaria treatment during the second and third trimesters of pregnancy where multi-drug resistance is likely. Whilst most of the data from treatment doses is from Asia, 287 pregnant women in the Gambia given a single dose of SP-artesunate had no increased rate of adverse birth outcomes (Deen *et al* 2001). Recent meetings of toxicologists and clinicians convened by the WHO (July 2002) reviewed all available data. Whilst there is some evidence of fetal toxicity in some animals early in pregnancy, there was felt to be no evidence from human studies contradicting proceeding with studies with artemisinin containing drugs in the second 2 trimesters of pregnancy (report in progress).

Amodiaquine also has been given to many hundreds of women in pregnancy in Africa and elsewhere, either inadvertently or deliberately, and studies have demonstrated no teratogenicity (Thet Naing *et al* 1988), although formal safety data are sparse. The WHO recommends it can be used for treatment of malaria in pregnancy (1995). Although formal side-effect studies on these combinations (SPAQ AQAS) have not yet been conducted, hence this proposal, there is sufficient data from pregnant women to justify the combinations chosen in a randomized trial which actively looks for side-effects and birth outcome in women where the drug is given after the first trimester.

Chlorproguanil-dapsone has recently proved effective as monotherapy in children in the Muheza district ([name] *et al* 2001). It is likely to be a relatively cheap antimalarial, and may be useful in pregnancy used as monotherapy, in combination therapy or in intermittent therapy in pregnancy. Whilst experience with chlorproguanil-dapsone in pregnancy is limited to use with a single dose, where it appeared safe (Keuter *et al* 1990), proguanil has been recommended for use as the safest antimalarial in pregnancy for many years. Experience with dapsone treatment during pregnancy used in Hansen's disease (Kahn 1985, Lyde *et al* 1997) and in other pregnancy related conditions (Lush *et al* 2000) is reassuring. There are theoretical reasons to be cautious of antifolates in pregnancy, but in the case of S/P (and co-trimoxazole) there has so far been little data to suggest they pose any hazard in the second and third trimesters of pregnancy (WHO 1986).

Study drugs will be purchased or sourced from reputable sources with Good Manufacturing Practice (GMP). Dosages will be based on the body weight (kg) of the patient and the schedule will be as below.

- (a) SP (sulfadoxine 25mg/kg stat)[SP];
- (b) SP (sulfadoxine 25mg/kg stat) + Amodiaquine (10mg/kg x 3 days) [SPAQ];
- (c) Chlorproguanil-dapsone (1.2 mg/kg and 2.4 mg/kg respectively 3 days) [Lapdap]
- (d) Amodiaquine (10mg/kg x 3 days) + Artesunate (4mg/kg x 3 days) [AQAS]

